## Abstract

**Clinical Trial Registration:**

https://ctri.nic.in/Clinicaltrials/pmaindet2.php?EncHid=MTQ2MTYw&Enc=&userName=, Registered in Clinical Trial Registry, India (CTRI/2025/12/098832- registered on 10-12-2025). Participant enrolment for the trial has commenced, and the study is currently ongoing.

## Introduction

1

### Background and rationale

1.1

Head and neck cancer arises from the epithelial lining of the upper aerodigestive tract and represents the seventh most common malignancy worldwide (1). Radiotherapy, either alone or in combination with concurrent chemotherapy, remains a cornerstone in the management of these malignancies (2). However, these treatment strategies are commonly associated with wide range of oral complications, including oral mucositis, secondary infections, xerostomia, dysgeusia, pain and an increased risk of dental and periodontal diseases. These complications impair essential activities like eating, swallowing, speaking and thereby reducing quality of life of patients. In severe cases, they may lead to treatment interruptions, infections and compromised oncological outcomes (3, 4).

Among the complications, oral mucositis (OM) is one of the most dose limiting toxicity of cancer treatment and it is featured by inflammation and ulceration of oral mucosa, typically developing 5–7 days after the initiation of chemo and radiotherapy. Approximately 40% of head and neck cancer patients receiving chemotherapy alone develop OM, whereas 90%–100% patients receiving concurrent chemo-radiotherapy (5). Evidence from Indian clinical settings indicated that radiation-induced oral mucositis (RIOM) usually appears after a cumulative radiation dose of approximately 20Gy, becomes more widespread at around 30Gy, and reaches peak severity with Grade 3 reactions at cumulative doses of 66 – 70Gy (6).

Despite high prevalence and clinical impact of RIOM, the effective curative therapies remain limited. Current management strategies are largely supportive and primarily focus on pain relief and symptomatic management. Conventional interventions include saline mouthwashes, topical anaesthetics, analgesics, cryotherapy, low level laser therapy and protective radiation fields (7, 8). Various pharmacological agents such as benzydamine hydrochloride, doxepin mouthwash and palifermin have been explored for mucositis prevention and treatment. Palifermin, the only US FDA approved drug for OM prevention, is primarily used for hematological malignancies due to high cost and has only 30% reduction in severe mucositis incidence (4, 9). Similarly, benzydamine, chlorhexidine and other anti-inflammatory or anti-microbial washes often provide temporary relief (10). Importantly severe OM frequently results in interruption or modification of cancer therapy, which may adversely affect treatment efficacy (11).

Recent studies have explored the beneficial role of plant-based medicines in the prevention and management of RIOM (12). In this context, the traditional systems of medicine practiced in India may offer promising integrative approaches for RIOM management. The Siddha system of medicine, one of the AYUSH systems traditionally practiced mainly in southern India, as well as in Sri Lanka and Malaysia, includes several therapeutic formulations for the treatment of oral ulcers and inflammatory conditions affecting the oral mucosa. Among these, *Triphala Chooranam* (TPC) mouth wash and *Gungiliya Vennai* (GV) topical application are traditionally indicated for mucosal healing and ulcer management (13, 14). Combining evidence-based Siddha interventions with standard oral care may provide integrative therapeutic approach that enhances mucosal protection, reduces treatment related toxicity and improves compliance in patients undergoing radiotherapy.

TPC, a polyherbal formulation containing *Terminalia chebula* Retz*.*, *Phyllanthus emblica* L*.*, and *Terminalia bellirica* (Gaertn.) Roxb*.*, has supportive evidence suggesting its potential role in the management of oral mucositis. Sruthi et al.*,* conducted a clinical trial among head and neck cancer patients undergoing chemo-radiotherapy demonstrated TPC mouth wash significantly reduced oral pain and associated features when compared to chlorhexidine mouth wash (15). Similarly, Suresh et al.*,* reported a significantly lower incidence of intolerable mucositis among patients receiving TPC mouth wash when compared to povidone iodine (16). GV, another Siddha formulation containing *Shorea robusta* C.F. Gaertn. resin, sesame oil and tender coconut water has demonstrated significant wound healing properties in pre-clinical studies. Bhat et al.*,* reported the topical application of this medicine significantly accelerated regeneration of adnexal skin in animal models indicating strong regeneration and tissue repair that may be beneficial in OM healing (17). Moreover, TPC and *Shorea robusta* C.F. Gaertn. have demonstrated favourable safety profiles in clinical and experimental studies (18–20).

In our previously documented case series (unpublished) involving seven patients, the use of above mentioned Siddha formulations over a period of 48 days, demonstrated notable therapeutic benefits. Summarising the report of that study, patients experienced an average 5-point reduction in pain on Visual Analogue Scale (VAS) and a 2-grade improvement in oral mucositis severity, as measured by WHO Mucositis Grading Scale. These findings suggest the potential value of these Siddha formulations as adjuncts to conventional therapy.

### Explanation for the choice of intervention

1.2

Considering the high prevalence and clinical burden of RIOM, along with limitations of currently available therapies, there is a need for safe, cost effective and accessible adjunct strategies. Preliminary evidences suggests that TPC and GV possess anti-inflammatory, muco-protective and safety advantages. However, systemic evaluation of their combined use as an adjunct to standard oral care in patients undergoing RT for head and neck remains limited.

Therefore, this study aims to assess the efficacy of a Siddha regimen, comprising TPC mouth wash and GV topical application, as an adjunct to standard of care (SOC), compared with SOC alone, proportionate reduction in the occurrence of severe RIOM, as assessed by the Radiation Therapy Oncology Group (RTOG) grading scale, during radiotherapy and 6 weeks post-radiotherapy, thereby generating scientific evidence to support integrating Siddha practices with SOC.

### Objectives

1.3

The primary objective of this study is to evaluate the proportionate reduction in the occurrence of severe RIOM, as assessed using RTOG grading scale, among participants receiving a Siddha regimen as an adjunct to standard care compared with those receiving standard care alone, assessed during radiotherapy and at six weeks post-radiotherapy.

The secondary objectives are to assess the proportionate reduction in the severity of radiation-induced oral mucositis using WHO oral mucositis scale at the same time points; to compare oral cavity pain intensity between the study groups using VAS, assessed weekly throughout the study period; to evaluate changes in analgesic usage, including escalation or de-escalation according to the WHO Three-Step Analgesic Ladder, on a weekly basis during the study period; to estimate and compare the proportion of adverse reactions between the study groups; and to evaluate differences in the frequency and duration of treatment interruptions attributable to oral mucositis between the study groups.

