### Outcomes

2.5

The primary outcome of the study is the severity of RIOM, assessed using RTOG grading scale. This will be measured as the proportion of participants who develop severe oral mucositis (RTOG grade ≥ 3) at any time during radiotherapy and up to six weeks following completion of radiotherapy, compared between the two study arms. The primary outcome will be assessed from randomisation until the last day of study medication use.

The secondary outcomes include oral mucositis severity assessed using WHO oral mucositis scale, measured as the proportionate reduction in the occurrence and severity of mucositis during radiotherapy and up to six weeks post-radiotherapy. Oral cavity pain, evaluated using VAS as the proportion of participants achieving a minimum two-point reduction in pain intensity and analgesic usage, assessed as the percentage of participants requiring analgesics categorised according to WHO three-step analgesic ladder. Safety outcomes will be evaluated by documenting the number of adverse events reported in each study group. Treatment interruption will be assessed as the proportion of participants experiencing one or more radiotherapy interruptions due to severe RIOM and the total number of days of missed radiotherapy. In addition, body weight changes during radiotherapy, requirement for nasogastric tube feeding, and interruptions in oral intake will be documented as exploratory indicators of nutritional impact. All secondary outcomes, except treatment interruption, will be assessed from randomisation until the last day of study medication use, while treatment interruption will be evaluated until the completion of radiotherapy.

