### Participant timeline

2.6

Participants will undergo initial screening and randomisation at baseline, followed by a 14-week observation period comprising weekly clinical evaluations and periodic laboratory assessments as detailed in the timeline below (Table 2).

**Table 2 T2:** Schedule of enrolment, interventions, and assessments.

Activity/Assessment	Baseline	W1	W2	W3	W4	W5	W6	W7	W8	W9	W10	W11	W12	W13
Enrolment														
Screening & Informed Consent	X													
Randomisation & Allocation	X													
Intervention														
Study Intervention	X	X	X	X	X	X	X	X	X	X	X	X	X	X
Efficacy Assessment														
RTOG Scale	X	X	X	X	X	X	X	X	X					X
WHO oral mucositis Scale	X	X	X	X	X	X	X	X	X	X	X	X	X	X
VAS		X	X	X	X	X	X	X	X	X	X	X	X	X
WHO 3-step analgesic ladder		X	X	X	X	X	X	X	X	X	X	X	X	X
Interruption of RT		X	X	X	X	X	X	X	X					
Days of Missed RT		X	X	X	X	X	X	X	X					
Safety & Laboratory Assessment														
Safety Monitoring		X	X	X	X	X	X	X	X	X	X	X	X	X
CBC	X								X					X
LFT	X								X					X
RFT	X								X					X

RT, radiotherapy; RTOG, Radiation Therapy Oncology Group; WHO, World Health Organization; VAS, visual analogue scale; CBC, complete blood count; LFT, liver function test; RFT, renal function Test; W1−13, No. of week.

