### Plans for assessment and data collection

4.1

Potential participants will be screened by trained investigators to ensure compliance with the inclusion and exclusion criteria. Screening will include a review of medical records and current radiotherapy or chemoradiotherapy details to confirm the diagnosis of head and neck cancer. Eligible participants will be informed about the study objectives, procedures, risks, and benefits, and written informed consent will be obtained prior to enrolment. All screening details will be documented in the screening form and case record form (CRF), with reasons recorded for screen failures. Participants meeting eligibility criteria will proceed to baseline assessments, randomisation, and initiation of the allocated intervention.

At the screening or baseline visit, detailed clinical and drug histories will be recorded. Clinical examination will then be performed to assess the oral mucositis severity using the RTOG and WHO Oral Mucositis Scales during baseline visit. Baseline laboratory investigations, including complete blood count (CBC), liver function test (LFT), and renal function test (RFT), will be performed. Participants will then be randomised, and study medications will be dispensed as per group allocation. Follow-up assessments will be conducted weekly by trained assessors throughout the course of radiotherapy, with telephonic follow-up continued up to six weeks post-radiotherapy. The severity of oral mucositis will be assessed using RTOG and WHO oral mucositis scales, pain intensity will be measured using a 10-point VAS, and analgesic use will be documented according to WHO three-step analgesic ladder. Details of the grading criteria for all these four scales are presented in Table 3. However, in certain clinical situations, analgesics, particularly opioids, may be prescribed for cancer-related pain rather than for RIOM. In such cases, the indication for analgesic use may not directly reflect RIOM severity. To address this, all analgesic usage will be documented along with the primary indication, and cases where analgesics are administered for non-RIOM-related pain, will be clearly specified with appropriate justification. All assessors and physicians involved in outcome evaluation will be trained in advance regarding grading scales and assessment procedures.

**Table 3 T3:** Assessment scales used for outcome evaluation.

Assessment Tool	Grade/Scale	Grading Description

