RTOG Oral Mucositis Scale	Grade 0	No change
	Grade 1	Irritation/ Mild pain not requiring analgesics
	Grade 2	Patchy mucositis with inflammatory serosanguinous discharge/ moderate pain requiring analgesics
	Grade 3	Confluent fibrinous mucositis/ severe pain requiring narcotic analgesics
	Grade 4	Ulceration, haemorrhage, or necrosis
WHO Oral Mucositis Scale	Grade 0	No oral mucositis
	Grade 1	Erythema and soreness
	Grade 2	Ulcers present & able to eat solid food
	Grade 3	Ulcers present& requires liquid diet due to mucositis
	Grade 4	Ulcers present; alimentation not possible due to mucositis
VAS for Oral Cavity Pain	0	No pain
	1–3	Mild pain
	4–6	Moderate pain
	7–10	Severe pain
WHO Three-Step Analgesic Ladder	Step 1	Mild pain; Non-opioid analgesics (paracetamol, NSAIDs) ± adjuvants
	Step 2	Mild to moderate pain; Weak opioids (e.g., codeine, tramadol) ± non-opioids and/or adjuvants
	Step 3	Moderate to severe pain; Strong opioids (e.g., morphine, fentanyl, oxycodone) ± non-opioids and/or adjuvants

To evaluate treatment response over time, the percentage distribution of grades/scores obtained from the four above mentioned scales will be assessed separately for each study arm at weekly intervals during study period. These assessments will help compare the severity of mucositis, recovery patterns, pain levels, and analgesic requirements between the two groups over the course of treatment and follow-up. Certain practical limitations may arise while applying the WHO oral mucositis scale in specific clinical situations. For example, some patients may already be receiving nutrition through a nasogastric (NG) tube due to tumour-related obstruction, poor nutritional status, or severe RIOM. In such cases, oral intake is restricted to liquids irrespective of the actual severity of mucositis, which could result in overestimation of the grade, such as categorizing the condition as Grade 3 despite the absence of corresponding clinical findings. To avoid such misclassification, these cases will be recorded as “Not Applicable” for WHO grading, along with proper justification in the study records.

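### The analgesic objective is change on the WHO ladder, but the outcome and analysis compare status by step, with no baseline step scheduled and no code for taking no analgesic

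*Protocol article*

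**What the plan says.** - **Objective (section 1.3).** One secondary objective is "to evaluate changes in analgesic usage, including escalation or de-escalation according to the WHO Three-Step Analgesic Ladder, on a weekly basis".
- **Outcome (section 2.5).** Analgesic use is to be "assessed as the percentage of participants requiring analgesics categorised according to WHO three-step analgesic ladder".
- **Analysis (section 4.5).** Ladder categories are compared between arms by a chi-square or Fisher's exact test. No escalation or change variable is named. The next sentence plans a separate comparison of rescue medication.
- **Schedule (section 2.6, Table 2).** The row "WHO 3-step analgesic ladder" is blank at baseline and marked at W1 to W13. The RTOG and WHO mucositis rows do have a baseline mark.
- **Baseline visit (section 4.1).** Only the two mucositis scales are named: "Clinical examination will then be performed to assess the oral mucositis severity using the RTOG and WHO Oral Mucositis Scales during baseline visit". However, "At the screening or baseline visit, detailed clinical and drug histories will be recorded".
- **Scale (section 4.1, Table 3).** The lowest ladder level is Step 1, described as "Mild pain; Non-opioid analgesics (paracetamol, NSAIDs) ± adjuvants". There is no level for no analgesic.
- **Indication (section 4.1).** The article recognises that "analgesics, particularly opioids, may be prescribed for cancer-related pain rather than for RIOM", and has the primary indication recorded with non-mucositis use specified and justified. Neither section 2.5 nor section 4.5 says how that flag enters the analysis.

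**The concern.** An objective about escalation needs a starting point and a level for every participant. Here the starting point is not scheduled, and the lowest level already presupposes a drug. The outcome that is defined answers a different question: how many participants are on each step, not how many moved.

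Some participants can be expected to enter on an analgesic. The exclusion criteria do not bar it, a post-operative radiotherapy subgroup is planned (section 2.2), and section 4.1 itself anticipates cancer pain treated with opioids. Under a status comparison their use is present from W1 whether or not mucositis develops. Randomisation is not stratified (section 3.1), so the arms may differ by chance in use at entry, and the plan provides no baseline step with which to account for it.

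At stake is whether this secondary outcome answers its objective, and with what precision. The primary outcome is not affected.

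**Working it through.** The article gives no figure to reproduce. The check is mainly a reading of sections against each other.

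**1. Objective against outcome against analysis.** Section 1.3 asks for movement on the ladder. Sections 2.5 and 4.5 give the distribution over steps and a between-arm test of it. Section 4.1 adds weekly percentage distributions for each arm, which again describe status. No section defines a within-participant change.

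**2. Schedule.** Table 2 has 14 columns (baseline plus W1 to W13). The WHO mucositis scale has 14 marks; the ladder has 13, with baseline blank. W1 does not replace baseline. It follows randomisation, and under section 2.4.1 the mouthwash starts on day 0 or, for some participants, on the day radiotherapy starts. Section 1.1 puts typical onset of mucositis at 5 to 7 days after therapy begins, so a W1 value may already reflect mucositis.

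**3. Levels.** In Table 3 the RTOG, WHO mucositis and VAS scales each have a 0 level; the ladder does not. With a no-analgesic level there would be 4 levels and 4 × 3 / 2 = 6 possible upward moves: none to 1, none to 2, none to 3, 1 to 2, 1 to 3 and 2 to 3. Three of the six start from no analgesic and have no code as tabulated. The same holds for the three downward moves that end in no analgesic. These are kinds of move, not frequencies.

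**4. What can and cannot be obtained.**

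| Quantity | As planned |
|---|---|
| Share on each step, by week, W1 to W13 | Yes |
| Week-to-week move among users after W1 | Computable, but not defined as an outcome |
| Start or stop of analgesics | Inferable from absence of use; no code in Table 3 |
| Change from a pre-treatment step | Not scheduled or planned; would have to be derived from the drug history |

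**5. Possible size, as illustration only.** The article gives neither analgesic use at entry nor expected need. Assume that a share b of participants use an analgesic at entry and remain users, and that a share p of the others come to need one. Any-use is then b + (1 − b)p, and a between-arm difference in p is multiplied by (1 − b).

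- Assume p = 0.60 against 0.45, a difference of 15 points.
- b = 0.30: 0.30 + 0.70 × 0.60 = 0.720 against 0.30 + 0.70 × 0.45 = 0.615, a difference of 10.5 points.
- b = 0.50: 0.800 against 0.725, a difference of 7.5 points.
- Chance imbalance in b at 0.30 with 80 per arm: SE = √(2 × 0.3 × 0.7 / 80) = 0.072, so about ±14 points (1.96 × 0.072).
- Effect of a 14-point imbalance on any-use: 14 × (1 − p), which is 5.6 points at p = 0.60 and 7.7 points at p = 0.45.

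These figures describe any use against none. The planned comparison is by step, so a participant who enters at Step 1 and rises to Step 3 still registers. The figures show the direction of the effect and are not an estimate for this trial.

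**The case against.** The strongest reply is that the objective says weekly change and does not say change from baseline. The ladder is recorded at every week from W1 to W13, so movement among users can be tracked, and a baseline step could be reconstructed from the drug history. A reader might infer that change cannot be computed at all; the documents do not support that. What stands is that no change variable is planned and no pre-treatment step is scheduled.

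Second, a percentage requiring analgesics implies non-users as the complement, and coding them as zero is ordinary CRF or analysis-plan detail. That is fair for the status outcome. For an escalation objective, the move from no analgesic to Step 1 is the most basic event, and the scale as tabulated has no place for it.

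Third, a reader might infer that analgesics for existing cancer pain will simply be counted as outcome. The documents do not say so. Section 4.1 records the indication and flags non-mucositis use, and the Discussion says such factors will be considered during analysis. The exact rule may properly sit in an analysis plan that is not shown. Nor does the reference in section 4.5 to overall analgesic requirements settle the matter, since it belongs to the separate rescue-medication sentence.

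Fourth, a reader might infer that a chance imbalance at entry carries over in full, or biases the result. Neither holds. In the illustration roughly half carries over, and under 1:1 randomisation this is random variation already reflected in the standard error.

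A full analysis plan could settle coding and the handling of indication. It would not add the missing baseline mark to Table 2 or make the stated outcome match the stated objective.

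**Conclusion.** The point holds in a limited form. The objective is change on the ladder, while the outcome and analysis are status by step. There is no scheduled baseline step, and Table 3 has no level for no analgesic. Followed as written, the plan does not measure change from a pre-treatment step.

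The consequence is a secondary outcome that only partly answers its objective, with noise and possible dilution from use already present at entry. The size cannot be stated because the article gives no baseline use. Under the assumed 30% to 50% use at entry, and the equally assumed 60% against 45% new need, a 15-point any-use difference would show as 10.5 to 7.5 points; the step comparison would be affected differently. No systematic bias is shown. The repair is nearly free and worth making while enrolment is under way.

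**What to change.** 1. **Table 2:** mark the ladder at baseline, filled from the drug history already taken in section 4.1. For participants already enrolled, derive the step retrospectively from that history.
2. **Table 3:** add a Step 0 for no analgesic.
3. **Sections 2.5 and 4.5:** define the outcome as change from the participant's own baseline step, for example the proportion escalating by at least one step. Alternatively, keep the step comparison and adjust it for baseline step. Base it on all-cause analgesic use.
4. **Supporting analysis:** repeat it for use indicated for mucositis, using the indication already recorded.

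The cost is one CRF field and revised wording, with no new procedure. There are two drawbacks. Participants who enter at Step 3 cannot escalate, so an escalation endpoint has a ceiling; adjusting for baseline step is the alternative if many enter that high. Attribution of an analgesic to mucositis is a judgement made in an open-label trial, which is why the indication-restricted analysis should support the all-cause analysis and not replace it.
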